**Cohort B:**

To obtain significant data in cohort B, we require paired pre- and post-measles PBMC of at least 50 children. This will allow statistical comparison of the precursor frequencies of circulating memory lymphocyte populations before and after measles.

Here, we need to take other uncertainties into account. Most importantly, it is a possibility that children that consent to collection of a pre-measles blood sample may decide to withdraw their consent for collection of a second sample. Historically, it has been observed that this occurs in approximately 50% of the children. An additional theoretical risk is that the school of the children does not become involved in the measles outbreak. However, observations from previous measles outbreaks in the bible belt suggest that this risk is low, especially since we intend to recruit children at schools with very low vaccination coverage. Finally, the detection of memory lymphocyte populations by flow cytometry will determine on the availability of suitable tetramers that can be used to stain these populations by flow cytometry. Tetramers are restricted to specific HLA-haplotypes, and thus technical limitations may result in the inability to detect memory lymphocytes in a specific patient.

As a result, we estimate that it will be necessary to collect a first blood sample of 100 children.

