**Cohort B** consists of unvaccinated children aged 6-13 years. These children will be recruited by contacting orthodox protestant schools with low vaccination coverage. Via the schools (groups 3-8) we will approach families that have not yet been exposed to MV, but live in an area that is expected to become part of the measles outbreak. One tube (maximum volume 9 ml) of heparinised blood will be collected; PBMC will be isolated and frozen. The parents will be contacted every two weeks by email or telephone, to monitor whether the children have contracted measles. Two to three weeks after the end of the measles outbreak in the school, a second 9 ml heparinised blood sample will be collected from the same children. This second blood sample will also be collected if the child did not experience measles during this outbreak. In this case the child will serve as an internal control: according to our hypothesis the frequency of pre-existing memory lymphocytes should remain stable in children that do not develop measles. However, we estimate the chances of unprotected children escaping from measles virus infection at a school with low vaccination coverage as minimal. The main

study parameter in this group will be the quantification of pre-existing memory lymphocyte populations in peripheral blood by tetramer staining, to test the hypothesis that these populations are decimated during measles.

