### **5.5 Replacement of individual subjects after withdrawal**

If parents have consented but children refuse to cooperate before any samples have been collected, the subject will be replaced. If samples have already been collected the subject will remain included.

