## 6. STATISTICAL ANALYSIS

In cohort A the outcomes will be presented as qualitative data: the percentage MV-infected cells within different white blood cell populations and subpopulations will be determined by flow cytometry. These data will be linked to the time point of sample collection, expressed as the number of days before or after onset of rash. To test our hypothesis that MV predominantly infects memory lymphocytes, the percentages MV-infected cells within the memory B-lymphocyte, memory CD4+ T-lymphocyte and memory CD8+ T-lymphocyte subpopulations will be compared with those in the naïve B-lymphocyte, CD4+ T-lymphocyte and CD8+ T-lymphocyte subpopulations, respectively. For this comparison we will use a paired t-test on log-transformed data. If the data are not normally distributed, a non-parametric test will be used for this comparison (Mann-Whitney U-test).

In cohort B the data will be presented as precursor frequencies of memory lymphocytes to infections unrelated to measles. The difference between these precursor frequencies before and after measles will be analysed by using a paired t-test on log-transformed data. If the data are not normally distributed, a non-parametric test will be used for this comparison (Mann-Whitney U-test). Patients or data will only be included if memory lymphocyte populations can be identified in the pre-exposure PBMC sample.

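### Cohort B: the 100 first samples are presented as covering three losses, but the stated refusal rate of about 50% uses up the whole allowance, so fewer than 50 analysable measles pairs are expected

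*Protocol*

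**What the plan says.** Section 1.4 of the protocol, under Cohort B, sets the requirement: "we require paired pre- and post-measles PBMC of at least 50 children". The next sentence ties that number to the statistical comparison of precursor frequencies before and after measles.

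The section then names three uncertainties to be taken into account:

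- Withdrawal of consent for the second sample: "Historically, it has been observed that this occurs in approximately 50% of the children".
- Schools: "An additional theoretical risk is that the school of the children does not become involved in the measles outbreak". The protocol calls this risk low.
- HLA restriction of the tetramers: "technical limitations may result in the inability to detect memory lymphocytes in a specific patient".

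The conclusion follows directly: "As a result, we estimate that it will be necessary to collect a first blood sample of 100 children".

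Two other places decide who counts in the comparison. Section 6 says: "Patients or data will only be included if memory lymphocyte populations can be identified in the pre-exposure PBMC sample". The Study Design section provides that a child who does not get measles is still sampled a second time, but "In this case the child will serve as an internal control".

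**The concern.** The number 100 is offered as the result of weighing three losses, yet it equals the requirement of 50 corrected for the first loss alone. Nothing in it is set aside for children whose memory cells cannot be stained, or for children who never become measles cases.

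Both groups drop out of the main cohort B comparison. A child without an identifiable memory population before exposure is excluded under section 6. A child who escapes measles gives a pair of samples, but a control pair.

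At stake is the stated basis for the cohort B size. A reader of section 1.4, including the ethics committee, would take it that 100 first samples should yield at least 50 analysable pairs. On the protocol's own refusal figure, that is not what they are expected to yield.

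**Working it through.** **Inputs from the protocol**

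- Required pairs: 50 (section 1.4, Cohort B).
- Refusal of the second sample: about 0.50 (same section).
- First samples: 100 (same section).
- Share of children in schools not reached, s: no rate given, called low.
- Share of children without a usable tetramer, h: no rate given.
- Alpha, power, effect size and SD for cohort B: not given.

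**Step 1: reproduce the stated figure.** First samples needed = required pairs / (1 - refusal) = 50 / (1 - 0.50) = 100. This matches the protocol exactly with refusal as the only loss.

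**Step 2: yield with refusal alone.** Expected pairs = 100 x 0.50 = 50. With X binomial (100; 0.50), P(X >= 50) = 0.54 and P(X > 50) = 0.46. So 50 is the mean of what 100 first samples deliver, before any other loss.

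**Step 3: add the other named losses.** Expected analysable measles pairs = 100 x (1 - 0.50) x (1 - s) x (1 - h). This is below 50 whenever s or h exceeds zero. With s = 0 and an assumed range for tetramer coverage (1 - h):

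| Tetramer coverage (assumed) | Expected pairs | P(at least 50) |
|---|---|---|
| 100% | 50 | 54% |
| 90% | 45 | 18% |
| 80% | 40 | 2.7% |
| 70% | 35 | 0.15% |
| 60% | 30 | 0.002% |

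With an assumed s = 5% as well, coverage of 80% gives 100 x 0.50 x 0.95 x 0.80 = 38 expected pairs, and the chance of at least 50 is 1.0%.

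**Step 4: sensitivity to the refusal rate.** The protocol says only approximately 50%. With no other loss, 45% refusal needs 50/0.55 = 90.9, so 91 first samples, and 55% refusal needs 50/0.45 = 111.1, so 112. With 40% refusal and 90% coverage, expected pairs are 100 x 0.60 x 0.90 = 54. With 45% refusal and 90% coverage they are 100 x 0.55 x 0.90 = 49.5.

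**Step 5: what fewer pairs mean for the comparison.** The protocol fixes no power, so this is an illustration for the paired t-test named in section 6, at two-sided 5% and 80% power. The detectable mean difference, in units of the SD of the paired log differences, is 0.40 at n = 50, 0.45 at n = 40 and 0.53 at n = 30.

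**The case against.** **The 50 refers to samples collected, not to pairs analysed.** The requirement is indeed worded as paired PBMC, and *analysable* is an inference. It is a sound one: section 1.4 ties the 50 to the statistical comparison and lists tetramer failure among the reasons that lead to 100. Even on the narrow reading, at least 50 pairs are reached with a chance of only 54%, and only if every school is reached and every child infected.

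**The other losses are small and the refusal rate is approximate.** Much of this stands. The protocol calls school loss low and escape from infection minimal, and section 7.4 expresses certainty that unvaccinated children in such schools will be infected. That leaves the tetramers as the main further loss, and the 60 to 90% coverage used above is an assumption of this review. If refusal came in at 40%, a 10% tetramer loss could be absorbed.

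**Stronger readings that the documents do not support.** A reader might infer that 50 is the best the plan can yield; it is the mean under refusal alone, with a 46% chance of exceeding it. A reader might infer that the analysis will certainly fall well short; the shortfall is an expected one of unknown size. A reader might take section 5.5 ("If samples have already been collected the subject will remain included") as a cap on cohort B recruitment. It concerns replacement of withdrawn subjects and sets no ceiling, and section 1.4 gives 100 as an estimate for this cohort, whereas cohort A has an explicit upper limit.

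**The consequence is modest.** This also stands in part. No precision is promised, so none is broken. If the effect is as large as the hypothesis suggests, fewer pairs may suffice: at an assumed paired effect of 0.8 SD, power with 30 pairs is 98.8%.

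**Conclusion.** The point holds as an internal inconsistency in section 1.4. The figure of 100 is exhausted by the first of the three losses that it is said to cover. At about 50% refusal, fewer than 50 analysable measles pairs are expected for any further loss above zero.

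The direction follows from the protocol's own figures; the size does not. Under assumed tetramer coverage of 90 down to 60%, with every school reached and every child infected, 45 down to 30 pairs are expected.

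This is a correction to the stated justification of the sample size. It does not show that the main cohort B comparison is compromised, because the protocol states no effect size or SD against which to judge that.

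**What to change.** Keep the 100 first samples and restate section 1.4 for cohort B:

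- Describe about 50 as the expected number of second samples collected at the stated refusal rate, and not as a minimum number of pairs for analysis.
- Give the expected number of analysable measles pairs, which is lower, as 100 x 0.50 x (1 - s) x (1 - h). The rates s and h should be the sponsor's own assumptions for school and tetramer loss, labelled as such and shown as a range.
- Give the detectable paired effect for that range, with the significance level and power used. The values of 0.40, 0.45 and 0.53 SD at 50, 40 and 30 pairs can serve as a pattern.

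The cost is wording only; no further children need to be sampled. Raising the number of first samples to 50 / (0.50 x coverage), which is 112 at 90% coverage and 167 at 60%, is not needed. It would reach 50 in expectation only: the chance of at least 50 would be about 57% and 54% respectively.

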## **2. TREATMENT OF SUBJECTS**

Not applicable

**2.1 Investigational product/treatment**

**2.2 Use of co-intervention (if applicable)**

**2.3 Escape medication (if applicable)**

**3. INVESTIGATIONAL PRODUCT**

Not applicable

- 3.1 Name and description of investigational product(s)**
- 3.2 Summary of findings from non-clinical studies**
- 3.3 Summary of findings from clinical studies**
- 3.4 Summary of known and potential risks and benefits**
- 3.5 Description and justification of route of administration and dosage**
- 3.6 Dosages, dosage modifications and method of administration**
- 3.7 Preparation and labelling of Investigational Medicinal Product**
- 3.8 Drug accountability**

**4. NON-INVESTIGATIONAL PRODUCT**

Not applicable

- 4.1 Name and description of non-investigational product(s)**
- 4.2 Summary of findings from non-clinical studies**
- 4.3 Summary of findings from clinical studies**
- 4.4 Summary of known and potential risks and benefits**
- 4.5 Description and justification of route of administration and dosage**
- 4.6 Dosages, dosage modifications and method of administration**
- 4.7 Preparation and labelling of Non Investigational Medicinal Product**
- 4.8 Drug accountability**

## 5. METHODS

### 5.1 Study parameters/endpoints

#### 5.1.1 Main study parameter/endpoint

**Cohort A:** the main study parameter of this cohort is the phenotypic characterization of MV-infected white blood cells by multicolour flow cytometry.

**Cohort B:** the main study parameters in this cohort are the identification of pre-existing memory lymphocyte populations in peripheral blood before MV infection (by tetramer staining in combination with multicolour flow cytometry) and the change in the frequency of these populations following MV infection.

#### 5.1.2 Secondary study parameters/endpoints (if applicable)

**Cohort A:** secondary study parameters in cohort A are the identification and characterization of cell-free and cell-associated virus, both in terms of quantity (what virus concentrations are present in the upper respiratory tract in relation to transmissibility of MV) and quality (what does transmissible MV look like under the electron microscope?). In addition, we will investigate what cytokines, chemokines and acute phase proteins can be measured in the plasma during the early stage of acute MV infection, in relation to the level of lymphopenia (reduced lymphocyte numbers in peripheral blood).

**Cohort B:** secondary parameters in cohort B are the measurement and characterization of MV-specific humoral and cellular immune responses. Massive expansion of MV-specific (and bystander) B- and T-lymphocyte populations is an essential characteristic of our immune suppression model, so we will investigate whether the quantitative and qualitative composition of the circulating lymphocyte pool of children after measles has indeed changed when compared to the pre-infection sample, while the composition of the paired samples of the control children remains essentially unaltered.

#### 5.1.3 Other study parameters (if applicable)

Not applicable

### 5.2 Randomisation, blinding and treatment allocation

Not applicable.

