## **8. ADMINISTRATIVE ASPECTS, MONITORING AND PUBLICATION**

### **8.1 Handling and storage of data and documents**

Data and materials will be labelled with an identification code. The key to that code will initially be safeguarded by the main investigator and will be transferred to an independent person to be kept for a longer period of time after initial processing of the data and materials. Handling of personal data will comply with the Dutch Personal Data Protection Act.

All clinical specimens that are stored will only contain the identification code, and will never contain names, initials or date of birth. Data tracking will be safeguarded by recording all stored samples in a digital freezer archive which is stored on a secured networkdrive of Erasmus MC. All samples belonging to this study will be made traceable by adding the keyword for the study (Bb2013) to each record.

The study does not involve detailed questionnaires. The only information recorded for subjects recruited to cohort A will be date of sampling, gender, age (in months), number of siblings and number of days before or after onset of rash. The only information recorded for subjects recruited to cohort B will be date of sample collection, date of onset of disease, gender, age (in months) and number of siblings.

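### Section 5.2 sets blinding aside entirely, yet the cohort B before/after flow-cytometry reading can be masked to time point and measles status, and nothing in the protocol does so

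*Protocol*

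**What the plan says.** Protocol section 5.2, "Randomisation, blinding and treatment allocation", deals with all three topics in one short answer: they do not apply.

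For cohort B, section 5.1.1 makes the main parameters the identification of pre-existing memory populations ("by tetramer staining in combination with multicolour flow cytometry") and the change in their frequency after infection. Section 6 fixes the comparison: "The difference between these precursor frequencies before and after measles will be analysed by using a paired t-test on log-transformed data". Section 6 also keeps a child or a result only if a memory population was identifiable in the sample taken before exposure.

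The Study Design section states the direction expected: a severe fall in children who get measles, and stability in those who escape it, who act as internal controls. It says of the first sample that "PBMC will be isolated and frozen". It does not say that the two samples of a child are stained, acquired or read together.

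Section 8.1 says "All clinical specimens that are stored will only contain the identification code", with no names, initials or birth dates, and that the main investigator initially keeps the key.

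**The concern.** Masking the person who reads an endpoint does not depend on there being a treatment to conceal. In cohort B the reader's result is the endpoint, the contrast is before against after, and the expected direction is stated in advance. If the reader knows which sample is which, and who had measles, the expected answer is known for cases and for controls.

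Two judgements are exposed. One is the frequency read in each sample. The other is whether a population is identifiable in the first sample, which decides whether the data enter the analysis.

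A small systematic difference in how the two samples are read appears as a within-child decrease. Among the measles cases, the paired test on its own cannot tell that from depletion. The same applies to a difference in handling if the first sample is frozen and later processed apart from the second.

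**Working it through.** **1. Is the reading masked anywhere?**

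- Section 5.2: blinding does not apply.
- Section 8.1: stored specimens carry a code that removes personal identifiers. The text does not say whether the code conceals time point or measles status, and does not present it as masking of the assay.
- Study Design, 5.1.1, 5.3 and 6: nothing on masked reading, fixed gates, a second reader or joint processing of pairs.

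**2. Which cohort is affected?**

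- Cohort B: two samples per child, before/after contrast, internal controls. Affected.
- Cohort A: one sample per child. Section 6 says the "percentages MV-infected cells within the memory B-lymphocyte, memory CD4+ T-lymphocyte and memory CD8+ T-lymphocyte subpopulations will be compared" with the matching naive subsets of the same child. There is no before/after contrast, so masking time point or status would not alter this comparison.

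**3. The protocol's own figure.** Section 1.4 asks for 50 pairs and expects about 50% not to give a second sample: 50 / (1 − 0.5) = 100 first samples, as stated. Masked reading leaves this unchanged. The protocol gives no alpha, power, SD or reader error, so the rest rests on assumptions.

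**4. How small a shift reaches significance?** Paired t-test on log data, n = 50, two-sided 5% (assumed). The critical t on 49 degrees of freedom is 2.010, so the observed mean change must exceed 2.010 / √50 = 0.284 SD. The apparent fall is 1 − exp(−0.284 × SD):

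| Assumed SD of within-child ln change | Apparent fall reaching p < 0.05 |
|---|---|
| 0.5 | 13% |
| 0.7 | 18% |
| 1.0 | 25% |

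**5. Chance of a spurious decrease.** No true change; post-measles samples under-counted by a fraction s. The noncentrality is −ln(1 − s) / SD × √50, and the probability is the upper tail of the noncentral t on 49 degrees of freedom beyond 2.010 (one direction, nominal 2.5%).

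For s = 0.10 and SD 0.7: 0.1054 / 0.7 × 7.071 = 1.064, giving 0.180. For s = 0.20: 0.2231 / 0.7 × 7.071 = 2.254, giving 0.599.

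| SD (ln) | 10% under-count | 20% under-count |
|---|---|---|
| 0.5 | 31% | 87% |
| 0.7 | 18% | 60% |
| 1.0 | 11% | 34% |

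**6. Cross-check on the log10 scale**, two-sided probability, assumed SD 0.2, 0.3 and 0.5: a 10% under-count gives 0.35, 0.18 and 0.10; a 20% under-count gives 0.92, 0.61 and 0.27. The picture is the same.

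**The case against.** Section 5.2 is a bundled template heading in an observational study, and its answer is true of treatment. It says nothing about the laboratory, and gating and batching details often sit in an analysis plan or laboratory procedure that is not shown. This has weight, but the section does name blinding and sets it aside without reservation, and no other section qualifies that.

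A reader might infer more than the protocol supports:

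- *That both primary endpoints are exposed.* Cohort A is not, for the reason in step 2 of the working.
- *That gates are set by hand by people who know time point and status.* The protocol does not say who gates or how, or what the reader knows. It only leaves this open.
- *That the code in section 8.1 reveals the time point.* The text is silent either way.
- *That reader bias could manufacture the predicted effect.* The hypothesis is of near-complete loss. A 10% or 20% shift would not resemble that; the risk is a modest fall that is nominally significant.

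The internal controls also count. Children who escape measles give a second sample, so a general before/after or batch shift would show in them too. However, the Study Design section expects very few of them, and they would not reveal a bias driven by known measles status.

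Finally, masking may be incomplete: the protocol predicts massive lymphocyte expansion after measles, which a reader may recognise. That limits the benefit but does not remove it.

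**Conclusion.** The point holds for cohort B only. Dismissing blinding is right for treatment and wrong for the reading of a before/after endpoint with a stated expected direction. Neither the reading nor the decision that a first sample is evaluable is masked by anything in the protocol.

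The size depends on the assumed SDs and under-counts, for which the documents give no figure. Across the range shown, the chance of a spurious significant decrease is 11% to 87% instead of 2.5%. These figures show how sensitive the test is to a reading difference; they are no evidence that one will occur. Because the remedy is cheap and uses samples that are collected anyway, the change should be made.

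**What to change.** In section 5.2, for cohort B, state the following:

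- Treatment blinding does not apply; laboratory reading is masked.
- The two samples of a child are cryopreserved alike, then thawed, stained and acquired in one run, under a code that conceals time point and measles status.
- Gating uses a prespecified template and is completed before the code is broken.
- HLA and tetramer selection, and the decision whether the pre-exposure sample is evaluable, are made and recorded before the post-measles sample is read. This work needs the first sample to be known as such, so it has to come first.

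Someone other than the reader should hold the key linking codes to time point and status.

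Cost: a recoding step and batching of pairs. Cohort B results wait for the second samples, and masking may be only partial. The numbers stay at 50 pairs and 100 first samples, with no additional blood from the children. Cohort A needs no change on this point.
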